**Figure 4 F4:**
[figure not shown]
**Example of a change-profile**.

### Process evaluation

It is impossible to control all external influences on performance, well-being and health from the implementation of the interventions until the follow-up measures. However, some actions will be taken to get insight into factors that possibly affect the results. Therefore, a process evaluation will be carried out [42]. The aim of this evaluation is to map factors that either stimulated or hindered successful implementation as well as the effectiveness of the interventions. The managers of the involved wards will be asked to note important changes and events on their wards in a logbook. Both after the first follow-up survey an the second follow-up survey, in-depth interviews will be held with the managers and nursing staff of both the intervention and comparison wards to interpret possibly changes in performance, well-being, and health on their ward. It will also be checked if employees on the intervention wards really perceived interventions. At the last page of both the follow-up surveys, they will be asked to list actions (since the previous survey) that were taken to improve health, well-being and performance on their ward. The same will be done with employees of the comparison wards. Consequently, it can be checked if managers of the comparison wards implemented interventions on their own initiative. In general, we will follow the intervention evaluation criteria as depicted by Scharf et al. [28] as much as possible.

### Procedure

At the base-line measure, each survey will be provided with a random chosen identification number corresponding to the employee. This number will be retained and used for the follow-up measures. The identification number is only available for the researchers and will be only used for analysis purposes. After completing, the employees can return the survey to the central researcher with a return envelope.

### Statistical analysis

#### Sample size calculation

Sample size calculation is based on emotional exhaustion, measured by the Dutch version [31] of the Maslach Burnout Inventory [32]. This measure is chosen because of the availability of norm scores for (certified) nursing assistant, which is the most occurring grade on both the intervention and comparison wards. The score ranges between 1 and 7, with an average score of M = 1.74 and a standard deviation of SD = 94. Setting alpha at 0.05, beta as 0.10 and Δ = .47 (half a standard deviation as a clinically minimal relevant difference [43] results in a required N = 120 (N = 60 for the experimental group and N = 60 for the comparison group) [44]. However, eight wards (N = 300) were interested to participate in the research project. Taking drop-outs into account, this sample is expected to be large enough to detect significant effects.

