## Methods and design

### Overview

The DIRECT-project (DIsc Risk Evaluating Controlled Trial) is a longitudinal, quasi-experimental field study (February 2009-February 2011) with a 'non-equivalent control group pretest posttest design' [27]. Employees within two Dutch nursing homes will participate in the research project, one in the North of the Netherlands and one in the South. In the nursing home in the North of the Netherlands two wards on one location will be the intervention group and two wards on another location will be the comparison group. In the Southern nursing home two wards will be the intervention group and two wards in the same location will be the comparison group. In total, four wards will be the intervention group (*n *= 150) and four wards will be the comparison group (*n *= 150). The more realistic terminology 'comparison group' was selected explicitly in contrast to 'control group' as the formal requirements for a real control group are not met [28]. Figure 1 presents a flow-chart of the design and measurements. Based on the result of the base-line survey (T1), workplace interventions will be implemented to optimize job demands, job resources, and recovery both during and after work time. One year after the baseline measurement, the results of the interventions will be evaluated by a follow-up survey (T2). To investigate if the interventions lead to enduring higher performance, well-being and employee health, a second follow-up survey will be conducted two year after the base-line measure (T3). In addition to the follow-up surveys, which will measure the effect of the interventions, a process evaluation will be performed.

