### Development of workplace interventions

Based on the results of the base-line survey the researchers will develop risk-profiles for each ward, which report the specific job demands, job resources, and recovery opportunities of the wards involved. Figure 2 presents an example of a risk-profile. It shows that particularly physical job resources and physical recovery are rather low to counteract the amount of physical job demands. The risk-profiles will be the starting-point for the researchers to generate ideas for workplace interventions that could be implemented to optimize job resources and recovery opportunities on the intervention wards. For developing and implementing interventions, a Participatory Action Research (PAR) approach will be used [38]. The philosophy behind PAR is that interventions designed to improve job-related outcomes cannot take place without the participation and experience of the subjects under study. The effectiveness of PAR in intervention research has been demonstrated empirically [39-41]. How will PAR be used in the present study? The results of the base-line survey together with the ideas for possible interventions from the researchers, will be discussed in small groups of employees from the experimental wards (i.e. intervention mapping). After consensus about interventions with the highest priority, employees will be made self-responsible for the implementation of (a part of) the interventions. During the process of developing and implementing interventions the researchers will be supported by an external consultant. How will the interventions look like? Figure 2 showed for example that the availability of physical job resources and physical recovery opportunities for this ward are rather low to counteract the relatively high physical job demands. To enlarge the amount of physical resources it can be important to check if there is sufficient adequate technical equipment to accomplish physically strenuous tasks and if this equipment is used correctly by the employees. Physical recovery at/after work can for example be improved by establishing fitness programmes or other sport and physical activities. To conclude, the ward-profiles will serve as the basis for the development of tailored ward-directed interventions. Figure 3 showed examples of workplace interventions based upon different kinds of job resources and recovery at/after work. All the interventions that will be implemented are primarily work-oriented rather than worker-oriented.

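### The sample of 300 is judged large enough from a calculation for independent nurses, although whole wards are allocated four against four; adequacy at 90% power is not supported

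*Protocol article*

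**What the plan says.** The Sample size calculation section of the Protocol article takes emotional exhaustion as its basis. Its settings are "Setting alpha at 0.05, beta as 0.10" and a difference of 0.47, described as "half a standard deviation as a clinically minimal relevant difference". The result is 120 in total, given as "N = 60 for the experimental group and N = 60 for the comparison group". The section continues "However, eight wards (N = 300) were interested to participate in the research project" and concludes "Taking drop-outs into account, this sample is expected to be large enough to detect significant effects".

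Other sections describe a ward-level design:
- Overview: two wards per group in each of two nursing homes. "In total, four wards will be the intervention group", with 150 staff, and four more form the comparison group, also with 150.
- Development of workplace interventions: risk profiles are drawn up per ward, and "the ward-profiles will serve as the basis for the development of tailored ward-directed interventions".
- Discussion: the wards are existing units, not randomised, and were chosen in matched pairs.
- Data-analysis: a multilevel repeated measures analysis is planned. The sample size section does not refer to it.

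**The concern.** Staff on one ward share the manager, the ward's events and, by design, the intervention. Their scores are therefore likely to be correlated, and each further nurse on a ward adds less information than an independent one would. The group contrast rests on eight wards, whereas the calculation counts individuals and has no term for this. The move from 120 to 300 looks like a 2.5-fold reserve, but its size cannot be judged without an ICC and a drop-out rate, and the article gives neither. Participation is voluntary and there are three surveys over two years, so fewer than 300 usable responses must be expected.

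At stake is how the result is read. If the adequacy sentence stands, a null finding could be taken as evidence against a half-SD effect under a 90% power premise that the design may not meet.

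**Working it through.** **Inputs from the article.** Alpha 0.05 (sidedness not stated; two-sided used), beta 0.10, difference 0.47. The text prints "a standard deviation of SD = 94"; since 0.47 is called half an SD, it is read as 0.94, so d = 0.5. Eight wards and 300 staff give m = 300/8 = 37.5 per ward and k = 4 wards per group.

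**Assumed, because not given.** ICC 0.02, 0.05 or 0.10; loss 0% or 30%; baseline to follow-up correlation r = 0.6.

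**1. The plan's own figure.** For independent nurses, n per group = 2(1.960 + 1.282)²/0.5² = 84.1, so 85 (86 with the exact t), or about 170 in total. One-sided, it is 69. With 60 per group, power is 78% two-sided or 86% one-sided. The 120 is not reproduced by either test and contains no hidden allowance for clustering.

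**2. Design effect.** DE = 1 + (37.5 − 1) × ICC = 1.73 / 2.83 / 4.65. Effective n per group = 150/DE = 87 / 53 / 32.

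**3. Power for a follow-up-only comparison.** In SD units, SE = √[2(ICC + (1 − ICC)/m)/4]. Power comes from the non-central t with non-centrality 0.5/SE on 8 − 2 = 6 df.

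**4. Power with baseline adjustment.** Multiply SE by √(1 − 0.6²) = 0.8 and use 5 df.

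**5. With 30% loss.** m = 0.7 × 37.5 = 26.25, or 105 per group.

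| ICC (assumed) | SE, full response | Power, 6 df | Power, adjusted, 5 df | 30% loss, 6 df | 30% loss, adjusted, 5 df |
|---|---|---|---|---|---|
| 0.02 | 0.152 | 78% | 90% | 69% | 84% |
| 0.05 | 0.194 | 58% | 73% | 52% | 68% |
| 0.10 | 0.249 | 39% | 53% | 37% | 50% |

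**6. Where 90% is reached.** At full response without adjustment, the ICC must be no more than about 0.006 on 6 df, or about 0.021 under a normal approximation that ignores the small number of wards. With 30% loss, the unadjusted 6-df test has 85% power even at ICC 0.

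**7. Ceiling with unlimited staff per ward.** SE tends to √(2 × ICC/4) = 0.100 / 0.158 / 0.224. Unadjusted power on 6 df then tends to 98% / 75% / 47%.

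**8. Pairing.** Four matched pairs analysed as pairs leave 3 df. If pairing removed no variance, the unadjusted full-response figures would be 60% / 43% / 29%. Any variance removed by the matching would offset this, but the article does not quantify it.

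**The case against.** The strongest reply is that every low figure depends on an ICC that the reviewer chose. At ICC 0.02 with full response, the normal approximation gives 91%, and baseline adjustment on 5 df gives 90%. This stands: a reader might infer that 300 is shown to be too few, and the documents do not support that, because they contain no ICC or drop-out rate from which to show it.

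Second, the follow-up-only figures do not match the planned analysis. The Data-analysis section plans repeated measures, and the Procedure section keeps identification numbers across waves. This also stands, so the baseline-adjusted column is the closer guide. It too depends on unstated inputs. With an assumed correlation of 0.8 for the ward component and 0.6 for the individual component, SE = √[2(0.36 × ICC + 0.64 × (1 − ICC)/37.5)/4] = 0.109 / 0.131 / 0.160, and power on 5 df is about 95% / 86% / 70%.

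Third, a reader might infer that recruiting more staff per ward could never help. The ceilings in step 7 show otherwise: in the unadjusted comparison it fails at 0.05 and above, but at 0.02 it could restore 90%.

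Fourth, the adequacy sentence is hedged and does not itself name 90%. That is correct. However, beta of 0.10 is the only standard the section sets, and the sentence follows directly from it.

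Finally, the wards are fixed and the baseline survey is done. That limits the remedy to the stated justification but does not make the justification sound. A multilevel analysis may handle clustering if ward is a level, but it does not repair a power claim made without it.

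**Conclusion.** The point holds as lack of support. The adequacy statement rests on an individual-level calculation that does not fit allocation of whole wards, and the 120 in that calculation is too low for its own inputs even for independent staff (about 170 two-sided). Whether 300 staff on eight wards give 90% power depends on quantities the article does not state. On the analysis closest to the plan, power runs from about 90% at ICC 0.02 to 53% at 0.10 with full response, and from 84% to 50% with 30% loss. These figures assume the ICCs, r = 0.6 at both levels, equal ward sizes, a two-sided test and 5 df. The error in the 120 needs no assumption about ICC or loss and persists under either sidedness.

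**What to change.** Replace the adequacy sentence with a ward-based statement for emotional exhaustion at the 12-month survey (T2). It should use eight wards of about 37 staff, a stated ICC range, stated response and drop-out rates, the baseline correlation, and a t reference on ward-level degrees of freedom that reflects the pairing described in the Discussion. Report power for half an SD, or the minimum detectable difference, across that range. State for which ICCs 90% power is reached, and claim no adequacy outside them.

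In the same section, correct the 120 to about 170 in total for independent staff (two-sided), state the sidedness, and print the SD as 0.94.

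The cost is one recalculation and a less favourable stated power. No extra wards or staff are needed.

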#### Drop-outs

Drop-outs will be documented thoroughly and included in the data-analysis to the point of drop-out. Analysis according to the guidelines by Goodman and Blum [45] will be conducted to assess any attrition effects. For instance, mean differences on measures from the base-line survey between those who responded and did not respond to the follow-up surveys.

#### Data-analysis

Cross-sectional, baseline, relations between specific types of job demands, job resources, recovery and job-related outcomes will be tested with hierarchical regression analysis (SPSS for Windows) and structural equation modeling (LISREL for Windows). In order to analyze causal associations within the two different waves, structural equation modeling (LISREL for Windows) will be used, as this technique is more useful to 'prove' causation (i.e. to rule out alternative, causal, assumptions). To evaluate the results of the interventions after the follow-up measures, multilevel repeated measures analysis will be performed using MLwiN. This technique has several advantages compared to repeated measures MANOVA, like the inclusion of cases with incomplete data and less restrictive missing data assumptions.

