Besides the obvious strengths of the present study, there are also some limitations. First, the design of the study is not a true experimental design. The wards participating in the present research project are existing organization units. Due to ethical and practical drawbacks, randomization is difficult to realize. However, the experimental- and comparison wards were selected in pairs so each intervention department has a similar comparison department. According to Ovretweit [46] 'Traditional experimental evaluation design is not well suited to investigating social systems or the complex way in which interventions work with subjects or her environment' (p99). Secondly, It is impossible to control all external influences on performance, well-being and health from the implementation of the interventions until the follow-up measures. To overcome this problem a thoroughly process evaluation will be conducted to detect and interpret external influences.

Although the limitations, the design of the present study is a feasible method to assess the effect of optimizing job demands, job resources, and recovery on health, well-being and performance related outcomes. The study is in progress. The baseline paper-and-pencil survey was conducted in the Spring of 2009. Interventions will be developed and scheduled to be implemented within due course. Follow up measurements are planned in 2010 and 2011, respectively. Dissemination of results is planned for the end of 2011.

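### A two-wave structural equation model cannot rule out alternative causal explanations as claimed; the planned third wave would let one main rival be fitted

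*Protocol article*

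**What the plan says.** The Data-analysis section of the protocol article sets out three strands of analysis.

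- **Baseline relations:** cross-sectional, by hierarchical regression and SEM.
- **Causal relations over time:** "In order to analyze causal associations within the two different waves, structural equation modeling (LISREL for Windows) will be used". The reason given is "as this technique is more useful to 'prove' causation (i.e. to rule out alternative, causal, assumptions".
- **Intervention effect:** "To evaluate the results of the interventions after the follow-up measures, multilevel repeated measures analysis will be performed using MLwiN".

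The Overview plans three measurements: a baseline survey (T1), then "One year after the baseline measurement, the results of the interventions will be evaluated by a follow-up survey (T2"), and finally "a second follow-up survey will be conducted two year after the base-line measure (T3"). The SEM sentence thus covers one wave fewer than the study collects, and it does not say which two it means.

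The Discussion concedes that "the design of the study is not a true experimental design" and that "Due to ethical and practical drawbacks, randomization is difficult to realize". According to the Measures section, job demands, resources, recovery and all outcomes are questionnaire scales in the same baseline and follow-up surveys.

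**The concern.** The claim concerns what the technique can do, so no further detail in a fuller plan would make it right. The word *prove* stands in the authors' own quotation marks and the phrase is comparative. The parenthesis that follows is not hedged: it says that alternative causal assumptions are ruled out.

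For non-randomised variables reported by the same person in the same survey, the obvious rival explanation is a stable disposition, response style or work setting that raises or lowers both the predictor and the outcome. If two waves cannot be tested against that rival, a significant path from, say, emotional resources at T1 to emotional exhaustion at T2 does not separate it from a causal effect.

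At stake is how the study's findings on the DISC Model are worded and believed. Paths that confounding can produce would be reported as evidence that resources or recovery cause better outcomes.

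**Working it through.** The article states no figure for the SEM, so there is none to reproduce. Its only computed number, the sample size, belongs to the comparison of emotional exhaustion between groups and plays no part here.

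**Step 1: can two waves test the rival?** Take one predictor X and one outcome Y. The article does not name the path model; I assume the usual cross-lagged form.

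| | Two waves | Three waves |
|---|---|---|
| Variances and covariances | 4 × 5 / 2 = 10 | 6 × 7 / 2 = 21 |
| First-wave variances and covariance | 3 | 3 |
| Autoregressive and cross-lagged paths | 4 | 8 |
| Residual variances and covariances | 3 | 6 |
| Degrees of freedom without stable components | 10 - 10 = 0 | 21 - 17 = 4 |
| Stable person components (2 variances, 1 covariance) | 3 | 3 |
| Degrees of freedom with stable components | 10 - 13 = -3 | 21 - 20 = 1 |

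With two waves the model is saturated, so its fit speaks against no alternative, and the rival is not identified. With three waves the rival can be fitted. Modelling the scales as latent variables with several items makes the measurement part testable, but the structural part among the four latent variables stays saturated.

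**Step 2: what path appears when there is no causal effect?** Let each variable be a stable person part (share *c* of the variance, correlation *r* between the stable parts of X and Y) plus a within-person part (autoregression *a*, within-wave correlation *w*). The true cross-effects are zero. Then

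- within-wave correlation: ρ = c·r + (1 - c)·w
- correlation of X1 with Y2: κ = c·r + (1 - c)·a·w
- stability: τ = c + (1 - c)·a
- standardised cross-lagged path: β = (κ - ρτ) / (1 - ρ²)

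None of *c*, *r*, *a* and *w* is in the documents, so all are assumptions. N = 300 is the article's number of interested staff before drop-out. The test is a two-sided Wald test at 5%.

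Worked example, c = 0.5, r = 0.5, a = w = 0: ρ = κ = 0.25, τ = 0.5, so β = (0.25 - 0.125) / (1 - 0.0625) = 0.133. The coefficient of Y1 is (0.5 - 0.25 × 0.25) / 0.9375 = 0.467, so R² = 0.5 × 0.467 + 0.25 × 0.133 = 0.267. The standard error is √(0.733 / (300 × 0.9375)) = 0.051, so z = 2.6 and the test rejects in about 74% of studies.

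| Stable share c | Correlation r | a | w | Spurious β | False positives |
|---|---|---|---|---|---|
| 0 | any | 0 or 0.3 | 0 or 0.2 | 0.000 | 5% |
| 0.5 | 0 | 0 | 0.2 | -0.051 | 17% |
| 0.3 | 0.3 | 0.3 | 0.2 | 0.016 | 6% |
| 0.5 | 0.5 | 0.3 | 0.2 | 0.060 | 25% |
| 0.5 | 0.5 | 0 | 0 | 0.133 | 74% |
| 0.5 | 0.7 | 0.3 | 0.2 | 0.110 | 61% |
| 0.5 | 0.7 | 0 | 0 | 0.199 | 97% |
| 0.7 | 0.7 | 0 | 0 | 0.193 | 99% |

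Over c = 0.3 to 0.7, r = 0 to 0.7, a = 0 or 0.3 and w = 0 or 0.2, β runs from about -0.05 to 0.20 and the false-positive rate from 5% to 99%. Simulation (N = 300, 400 replicates) at c = 0.5, a = 0.3, w = 0.2 agreed: β 0.063 with 26% rejections at r = 0.5, and β 0.106 with 60% at r = 0.7.

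**Step 3: the extreme case.** If one identical trait drives both variables (r = 1) and nothing else carries over, all correlations equal s and β = (s - s²) / (1 - s²). This gives 0.21 / 0.91 = 0.231 at s = 0.3 and 0.25 / 0.75 = 0.333 at s = 0.5.

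**Step 4: does the third wave help?** A three-wave cross-lagged model with stable person components, fitted to the same kind of data, recovers a cross-effect of 0.000 in the population. At N = 300 (150 replicates) the mean estimate was -0.003 to -0.007, with an SD of about 0.09.

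**The case against.** **SEM does allow rival models to be compared.** It can set forward, reversed and reciprocal paths against each other, and the authors may mean no more than that. This stands in part: a two-wave panel says more about direction than cross-sectional regression does. But all those models leave out stable person differences, so choosing among them does not exclude that rival. In the worked example the spurious path is 0.133 in both directions.

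**The wording is softened and the limits are admitted.** The quotation marks and the Discussion's remarks on design are real. They do not withdraw the parenthesis.

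**The magnitude is assumed.** This stands. Without a stable component, or with both correlations at zero, there is no bias. The values 0.23 and 0.33 require a scale to correlate with itself a year later no more strongly than with a different construct, so they are an upper end and not typical.

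A reader might infer four stronger points, which the document does not support.

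- *The intervention effect is compromised.* It is not: that effect is assigned to the multilevel repeated measures analysis.
- *The interventions rest on these paths.* They are built from the existing DISC principle and the ward risk-profiles of the baseline survey, before any follow-up data exist.
- *T3 is dropped.* T3 is collected and used for change-profiles, and nothing excludes it from the multilevel analysis. Only the SEM sentence speaks of two waves.
- *Both arms are pooled without arm or ward in the SEM.* The article is silent on this, and a condensed article may leave such detail to the full plan.

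**Conclusion.** The point holds as a wrong statement of what the planned SEM can establish. Two waves of non-randomised, same-survey self-reports cannot rule out stable differences between persons. In the usual bivariate form the model has no degrees of freedom with which to test them, and the rival model is not identified. Significant paths can therefore arise without any causal effect. How often depends on quantities that the documents do not give: from the nominal 5% up to 99% at N = 300 over the assumed range, and 25% to 74% at a stable share and correlation of 0.5.

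The article also needs to reconcile the two waves in the SEM sentence with the three in the Overview. The consequence is confined to claims about DISC-Model relations. The result rests on the assumption that the unnamed two-wave model is of the cross-lagged type.

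**What to change.** 1. In the Data-analysis section, delete the claim that SEM serves to prove causation or to rule out alternatives, and describe the paths as longitudinal associations.
2. State which waves enter the SEM. Use T1, T2 and T3 with a stable person-level (random intercept) component.
3. Account for study arm in that model, because the intervention falls between T1 and T2 and is meant to shift resources, recovery and outcomes in the intervention wards.

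The first change costs nothing, and the second uses data already planned. The price is precision: with an SD of about 0.09 at N = 300, a path must reach about 1.96 × 0.09 = 0.18 to be significant, and more after drop-out. With 1 degree of freedom in the bivariate case, the model is only weakly testable. Time-varying confounding remains, so the wording must stay associational even with three waves.

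### The intervention test does not name ward as a level or allow for having only eight wards, so control of its 5% error rate cannot be confirmed

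*Protocol article*

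**What the plan says.** The Overview section compares four intervention wards with four comparison wards in two nursing homes, with 150 staff planned per group. The section on developing the interventions has them tailored to each ward. The Discussion says that the wards are existing units, were not randomised and were chosen in pairs.

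For the effect of the interventions, the Data-analysis section states: "To evaluate the results of the interventions after the follow-up measures, multilevel repeated measures analysis will be performed using MLwiN". The reason follows: "This technique has several advantages compared to repeated measures MANOVA, like the inclusion of cases with incomplete data and less restrictive missing data assumptions". No levels are listed, and ward is not mentioned.

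The Sample size calculation section sets "Setting alpha at 0.05, beta as 0.10 and Δ = .47", described as "half a standard deviation as a clinically minimal relevant difference", and arrives at a "required N = 120 (N = 60 for the experimental group and N = 60 for the comparison group". It then adds: "However, eight wards (N = 300) were interested to participate in the research project". It gives no intraclass correlation (ICC) and no design effect.

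**The concern.** Staff on one ward share managers, events and, here, the intervention itself. The Process evaluation section expects this: managers are to log ward changes and events because these may affect the results. Ward-specific change between surveys is the variance against which a ward-level intervention has to be judged.

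The stated reasons for the multilevel model (cases with incomplete data, weaker missing-data assumptions, a contrast with repeated measures MANOVA) are the usual reasons for modelling occasions within persons. Together with a sample size for independent individuals, they leave nothing in the article that points to a ward level. If ward is left out, ordinary differences in change between wards can appear as an intervention effect. If it is put in but tested as though there were many wards, part of the problem remains. The article's research question rests on this comparison.

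**Working it through.** **The plan's own figure.** The SD is printed as "a standard deviation of SD = 94"; 0.94 is implied, because 0.47 is half an SD. With n per group = 2(z₁ + z₂)²(SD/Δ)²:

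- Two-sided 5%, 90% power: 2 × (1.960 + 1.282)² × (0.94/0.47)² = 2 × 10.51 × 4 = 84.1, so 85 per group.
- One-sided: 2 × (1.645 + 1.282)² × 4 = 68.5, so 69 per group.

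The stated 60 per group does not reproduce; it gives 78% power two-sided. That is a separate matter. What counts here is that neither the formula nor the stated result has a term for ward.

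**Inputs for the error rate.** Eight wards, four per group; 300/8 = 37.5 staff per ward. The article gives no dropout rate, so 30% loss is taken as an illustration (26.25 per ward). It gives no ICC either, so 0.02, 0.05 and 0.10 are assumed for the ward ICC of change.

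**Ward left out.** Design effect DE = 1 + (m − 1) × ICC. Type I error = 2 × [1 − Φ(1.96/√DE)].

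| ICC | DE, m = 37.5 | Type I error | DE, m = 26.25 | Type I error |
|---|---|---|---|---|
| 0.02 | 1.73 | 13.6% | 1.51 | 11.0% |
| 0.05 | 2.83 | 24.4% | 2.26 | 19.3% |
| 0.10 | 4.65 | 36.3% | 3.53 | 29.7% |

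A ward random intercept alone would not help the group-by-time test. A constant ward effect cancels from change, so the relevant variance is ward-by-time.

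**Ward effect included.** Simulation of 400,000 replicates per setting, balanced, unpaired, no true effect, m = 37.5. The simulated contrast is one group difference on one score per person, read here as the change score:

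| Test | ICC 0.02 | ICC 0.05 | ICC 0.10 |
|---|---|---|---|
| Maximum likelihood, z | 9.6% | 12.5% | 13.6% |
| Restricted ML, z | 7.3% | 9.0% | 9.6% |
| Maximum likelihood, t on 6 df | 4.1% | 6.3% | 7.4% |
| Restricted ML, t on 6 df | 3.0% | 4.2% | 4.8% |
| t test on eight ward means, 6 df | 5.0% | 4.9% | 5.0% |

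The z results agree with theory. As ward variance comes to dominate, restricted ML with z tends to 2P(t₆ > 1.96) = 9.8%. Maximum likelihood divides by 8 instead of 6 and tends to 2P(t₆ > 1.96 × √(6/8)) = 14.1%.

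**Power of a valid test.** With all 300 staff, an effect of half an SD of the analysed score and t on 6 df (critical value 2.447), effective n per group = 150/DE and the noncentrality is 0.5 × √(effective n/2):

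| ICC | Effective n per group | Noncentrality | Power |
|---|---|---|---|
| 0.02 | 86.7 | 3.29 | 78% |
| 0.05 | 53.1 | 2.58 | 58% |
| 0.10 | 32.3 | 2.01 | 39% |

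Treating the 300 as independent gives 99%.

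**The case against.** The strongest reply is that the article names a multilevel model, and such a model can carry a ward level. The listed advantages are introduced as examples, so silence on clustering does not rule it out. Levels, estimator and degrees of freedom are often left to an analysis plan, and this is a condensed journal article. The error rates also need an ICC that the article does not give.

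Much of this stands. A reader might infer that no planned analysis handles ward clustering and that false positives will be well above 5%. The article does not support that: it does not exclude a ward level, and restricted ML with a t test on 6 df holds the error at or below 5%.

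A reader might also extend the point to the baseline relations, which "will be tested with hierarchical regression analysis (SPSS for Windows) and structural equation modeling (LISREL for Windows", and to the between-wave modelling. That does not follow either. Those analyses examine associations between measures taken on individuals, not the allocated intervention effect, so these error rates do not carry over. Ward indicators or centring there would be a modelling choice.

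The reply does not dispose of the main point. The article gives reasons for its model and leaves clustering out of them, and it sizes the study as if staff were independent. The ordinary ways of carrying out what is written (occasions within persons, or a ward level with the usual z test) are both too liberal with four wards against four.

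**Conclusion.** The point holds in conditional form. Ward is the unit of allocation and intervention, but it is absent from the stated rationale for the effect analysis and from the sample size, and nothing addresses inference from eight clusters. At assumed ward ICCs of change of 0.02–0.10, type I error runs from about 11% to 36% if ward is omitted. At 37.5 staff per ward it is about 7% to 14% if a ward effect on change is fitted and tested with z.

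These sizes rest on the assumed ICCs, equal ward sizes, a single change score and unpaired wards. A smaller ICC shrinks them: at 0.01 and 37.5 per ward, omitting ward still gives 9%.

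**What to change.** Before the follow-up data are analysed, state in the Data-analysis section:

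- **Model.** Occasion within person within ward, with a ward-level random effect on change and not only on the intercept.
- **Estimation.** Restricted maximum likelihood (RIGLS in MLwiN).
- **Test.** Group-by-time against t with ward-level degrees of freedom, chosen in advance: 8 − 2 = 6 if wards are treated as unpaired, 8 − 3 = 5 with nursing home as a covariate, or 4 − 1 = 3 if the four ward pairs are analysed.
- **Check.** A t test on the eight ward mean changes, reported beside the model.

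The Sample size section should acknowledge clustering and give power over a range of ICCs.

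The change itself costs a few sentences and some extra modelling. The statistical cost is real and should be stated: confidence intervals widen, and power with 6 df and all 300 staff is about 78%, 58% or 39% at ICC 0.02, 0.05 or 0.10, before dropout. Using 3 df raises the critical value from 2.447 to 3.182, so pairing pays only if the pairs are well matched on change.
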